### **11.3 Sample Size and Power**

The Lane *et al* study was based on  $n = 52$  patients with chronic schizophrenia. They reported a Cohen's effect size ( $d$ ) of 1.53. Our patients (early psychosis) tend have slightly lower mean PANSS total scores (65.0), with a standard deviation of 14.3 units and it is anticipated that the effect size will be smaller in this group. With an alpha value of 0.05, and power of 0.8, we wish to be able to confidently detect a difference in mean PANSS Total of at least 7 units. This will require 66 participants per group ( $n = 132$ ). Over a 12 week period we predict attrition of 15%. Thus, we will need to randomize approximately 160 subjects.

### **11.4 Statistical Analysis**

All data will be analysed using SAS 9.4. We will compare demographic and clinical differences between the groups at baseline (Fisher exact test for nominal variables and Mann-Whitney test or independent sample  $t$  test for continuous variables). Efficacy will be assessed according to standard Intention to Treat (ITT) analytic procedures (i.e. for those who do not complete the 12 week study period, we will carry forward their last observation on the study outcomes). Mean changes in clinical assessment will be assessed using mixed-model repeated-measure (MMRM) methods with treatment, week, and treatment-week interaction as fixed effects and intercept as the only random effect; baseline value will be the covariant. The MMRM analyses will be performed using the SAS PROC Mixed procedure.  $P$  values will be based on 2-tailored tests with significance levels of 0.05.

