### **Efficacy measures include:**

Positive and Negative Syndrome Scale (PANSS) total score will be used as the primary outcome measure which is a widely used scale for measuring symptom severity of patients with schizophrenia.

Secondary outcome measures will include the following clinical assessments:

- PANSS subscales including Positive, Negative and General Psychopathology.
- Global Assessment of Function (GAF) which is a numeric scale (1 through 100) used by mental health clinicians and physicians to rate subjectively the social, occupational, and psychological functioning of adults.
- Clinical Global Impression (CGI) which is used to measure symptom severity, treatment response and the efficacy of treatments in treatment studies of patients with schizophrenia.

- Hamilton Depression rating Scale-17items (HDRS) is a multiple item questionnaire used to provide an indication of depression, and as a guide to evaluate recovery.
- Australian Quality of Life Scale (AQOL) is a 15 item instrument that measures five broad domains: Psychological well-being, physical senses, social relationships, independent living, and illness.
- Patient Global Impression (PGI) is a global index that is used to rate the response of a condition to a therapy (transition scale).
- Opiate Treatment Index (OTI) is a structured interview designed to provide a measure of the effectiveness of drug treatments.
- International Physical Activity Questionnaires (IPAQ) provides a common instrument that can be used to obtain internationally comparable data on health-related physical activity.
- The “Simple Physical Activity Questionnaire” (SIMPAQ) measures physical activity. It has been designed for use in various populations including clinical samples with high levels of sedentary behaviour.
- The Physical Activity Questionnaire (PAQ) has been developed to assess attitudes. Specifically, assessing; general opinion on physical exercise, motivators and barriers to exercise.
- The Activity and Participation Questionnaire (APQ6) is a short 6 item measure designed to complement clinical assessment, to support dialogue between consumers and clinicians about recovery goals, and to allow monitoring of change over time at both individual and aggregated service levels.

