#### **11.2.2 Secondary**

12 week treatment of 1000mg (500mg BD) Sodium Benzoate treatment improves Positive and Negative Syndrome Scale (PANSS) subscales, Global Assessment of Function (GAF), Australian Quality of Life Scale (AQOL), The Activity and Participation Questionnaire (APQ6), Clinical Global Impression (CGI) and Hamilton Depression rating Scale-17items (HDRS) compared to individuals taking placebo.

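### APQ6, a secondary endpoint rated only at baseline and week 12, does not fit the carry-forward rule in section 11.4: early leavers are scored as zero change or not at all

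*Protocol*

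**What the plan says.** Section 11.4 calls the efficacy analysis intention-to-treat and defines it by a single rule: "for those who do not complete the 12 week study period, we will carry forward their last observation on the study outcomes". The rule names no scale as an exception and does not say whether a baseline rating may be carried forward. Mean changes are then analysed by "mixed-model repeated-measure (MMRM) methods with treatment, week, and treatment-week interaction as fixed effects and intercept as the only random effect", and "baseline value will be the covariant".

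APQ6 is a secondary objective in section 2.2 and a secondary endpoint in section 11.2.2, in the list that ends "The Activity and Participation Questionnaire (APQ6), Clinical Global Impression (CGI) and Hamilton Depression rating Scale-17items (HDRS) compared to individuals taking placebo". Table 1 marks APQ6 at week 0 and week 12 and nowhere between. PANSS, GAF, AQOL, CGI and HDRS are marked at baseline and at all six fortnightly visits from week 2 to week 12.

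Sections 7.7, 8.10, 9.2 and 9.3 describe how participants come to be withdrawn or to withdraw. None of them schedules an exit assessment. Section 11.3 states: "Over a 12 week period we predict attrition of 15"%, and gives about 160 participants to be randomised.

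**The concern.** Carrying forward the last observation presupposes that a person who leaves has usually been rated at least once on treatment. On the fortnightly scales that is mostly so. On APQ6 the schedule rules it out: whoever leaves before week 12 has a baseline rating and nothing else. The rule then fills the week-12 outcome with a value measured before any treatment.

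Two consequences follow. A block of participants in both arms is fixed at zero change, which pulls the estimated treatment effect toward zero. And if the arms lose different proportions while everybody who stays tends to improve, the arm with more leavers looks worse for that reason alone.

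This goes beyond the usual criticism of carry-forward on the fortnightly scales, because here no early leaver can have an on-treatment value. It also differs from detail left to a later analysis plan: section 11.4 states a rule, and that rule conflicts with the protocol's own schedule.

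**Working it through.** **Inputs from the protocol.** Difference to detect 7 and SD 14.3 (PANSS total), two-sided alpha 0.05, power 0.80, 66 per group, 132 in all, about 160 randomised 1:1, predicted attrition 15% (sections 11.3 and 11.4). APQ6 ratings at weeks 0 and 12 (Table 1).

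**Assumptions, not in the protocol.** The APQ6 effect size, the baseline to week-12 correlation, the common improvement, any difference in attrition between arms, and the treatment of APQ6 as a continuous, roughly normal score. The protocol gives no APQ6 scoring.

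**1. The plan's own figures.** The two-sample formula with 7 and 14.3 gives 66 per group and 132 in all, as stated. Allowing for attrition, 132 / 0.85 = 155.3, so 156, which agrees with approximately 160. The 15% and the 160 are therefore a sound base.

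**2. Number affected.** 0.15 × 160 = 24 early leavers, about 12 per arm if attrition is equal.

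**3. What the rule does to them.**
- Literal reading: last observation = baseline, so the change is 0 for all 24.
- Post-baseline values only: there is nothing to carry, so all 24 are missing and the comparison rests on 160 − 24 = 136 completers.

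**4. Attenuation under the literal reading.** With a fraction p set to zero change in both arms, the expected difference is (1 − p) × effect. At p = 0.15 the factor is 0.85. An assumed effect of 0.40 SD becomes 0.85 × 0.40 = 0.34 SD. Simulation with 80 per arm, correlations of 0.3 to 0.7 and common improvement of 0 to 0.5 SD gives the same 0.34.

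**5. Power.** In those simulations power falls by about 1 to 7 percentage points against a baseline-adjusted analysis of the observed week-12 values, for example 0.70 against about 0.75. As a second illustration, take the PANSS standardised effect D = 7 / 14.3 = 0.49 as a change-score effect with SD 1, q = 0.85 and 80 per arm. An arm whose completers have mean change μ has variance V(μ) = q(1 + μ²) − (qμ)² once leavers are set to zero. With comparator completers' mean change m, the standard error is √{[V(m) + V(m + D)] / 80}:
- m = 0: qD / SE = 0.416 / 0.147 = 2.83, power 0.81.
- m = 0.5: 0.416 / 0.152 = 2.73, power 0.78.
- Completers only: power 0.81. No attrition: 0.87.

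Most of the loss from 0.87 comes from losing participants; the carry-forward rule adds at most about 3 points here.

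**6. Unequal attrition with no true effect.** The spurious difference is the common improvement times the difference in attrition. For 10% versus 20%: 0.3 × 0.10 = 0.03 SD and 0.5 × 0.10 = 0.05 SD. Simulated type I error is then about 0.054 to 0.072, against about 0.05 using observed week-12 values. For a 13% versus 17% split it stays near 0.05.

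**7. Does the section 11.4 model still work for APQ6?** With one post-baseline visit, the fixed-effect columns (intercept, treatment, week, treatment-week, baseline) number 5 and have rank 3. The two week terms duplicate the intercept and treatment. With one record per person, the random intercept cannot be separated from the residual. What remains is week-12 APQ6 on treatment and baseline, an ordinary ANCOVA in which the treatment effect is estimable.

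**The case against.** Section 11.4 never says that baseline is to be carried forward as an outcome; it gives baseline the role of covariate. If carry-forward means post-baseline values only, the 0.85 factor and the spurious difference disappear. That is fair, and the text does not settle it. But the other reading leaves leavers without any APQ6 score, and the analysis described as intention-to-treat becomes completers-only for this endpoint. Neither reading gives a sound result.

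It can also be said that the root fault is blanket carry-forward, so replacing it everywhere would cure APQ6 too. Dropping the rule would remove the artificial zeros. It would still leave APQ6 leavers with no on-treatment APQ6 value, so a scale-specific method is needed in any case.

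The harm is modest, and that objection stands in full. The type I inflation requires an attrition imbalance and a common improvement that the protocol does not predict. Taking 0.40 SD as the right answer supposes that leavers share the completers' effect, which nothing in the protocol establishes.

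A reader might infer that APQ6 cannot be analysed under section 11.4 at all, or that the trial cannot answer its APQ6 objective. The documents do not support this: the model reduces to an estimable ANCOVA, and the attenuation is limited.

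A reader might also extend the point to PGI, which Table 1 rates at week 12 only. PGI is a secondary measure in section 6 but appears in neither section 2.2 nor section 11.2.2. As a transition scale it has no baseline, and so no change score for a model of mean changes to analyse. It deserves a clarifying note and is not part of the main claim.

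**Conclusion.** The point holds for APQ6. The carry-forward rule does not fit a scale rated only at baseline and week 12. It either sets the change to exactly zero for about 24 of 160 participants or leaves them unscored.

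The count rests on the predicted 15%, which is a forecast and not a planned or guaranteed figure. The factor of about 0.85 rests on the literal reading, equal attrition and leavers sharing the completers' effect. The spurious difference of 0.03 to 0.05 SD rests on the assumed 10% versus 20% split and 0.3 to 0.5 SD common improvement.

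The power loss is small, and one secondary endpoint is affected. The primary PANSS total is rated every two weeks and is not affected by this point. The correction is worth making because the written rule gives a wrong answer for a named endpoint and is cheap to change.

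**What to change.** In section 11.4, exempt APQ6 from carry-forward. Analyse the week-12 value adjusted for baseline by ANCOVA, or by the ordinal equivalent if the scoring requires it, without the redundant week terms and random intercept. Handle early leavers by multiple imputation that uses the fortnightly GAF, AQOL and PANSS scores already collected. The cost is a sentence or two in section 11.4 and one extra imputation step.

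Optionally, add a footnote to Table 1 for an APQ6 rating at the last contact of an early leaver who still consents to assessment. Use it as auxiliary information in the imputation and not as a week-12 value. That means one short extra rating for at most about 24 people.

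For PGI, a note is enough that carry-forward and the baseline-adjusted repeated-measures model do not apply to it.

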## 1003 **9 Participant Completion and Withdrawal**

### 1004 **9.1 Participant Completion**

1005 Participants are considered to have completed the study if they complete 12 weeks of dosing.

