## **11 Data Analysis and Statistical Considerations**

### **11.1 Hypotheses**

Those participants allocated to the active arm (1000mg (500mg BD)) Sodium Benzoate treatment will have significant reductions in PANSS total score at week 12 compared to individuals taking placebo.

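### Section 11.4 pairs last observation carried forward with an MMRM; on the natural reading, dropouts' frozen scores enter the week-12 comparison and generally bias it if dropout differs by arm

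*Protocol*

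**What the plan says.** Section 11.4 equates intention to treat with a filling rule: "for those who do not complete the 12 week study period, we will carry forward their last observation on the study outcomes". The next sentence gives the model: "Mean changes in clinical assessment will be assessed using mixed-model repeated-measure (MMRM) methods with treatment, week, and treatment-week interaction as fixed effects", with "intercept as the only random effect; baseline value will be the covariant". No other efficacy model is named. The protocol neither restricts the MMRM to observed data nor labels carrying forward a sensitivity analysis.

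The hypothesis in section 11.1 concerns "significant reductions in PANSS total score at week 12 compared to individuals taking placebo", so the week-12 contrast is the one that matters. Section 9.1 defines who counts as a completer: "Participants are considered to have completed the study if they complete 12 weeks of dosing". Non-completers are expected. Section 11.3 states "Over a 12 week period we predict attrition of 15" per cent, and section 9.2 withdraws participants for, among other reasons, seven consecutive days of non-compliance or a serious adverse event assumed to be associated with study medication. PANSS total is scheduled at baseline and at weeks 2, 4, 6, 8, 10 and 12 (Table 1).

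**The concern.** A likelihood-based MMRM already uses every observed visit of a participant who leaves early, and it is valid if dropout is missing at random. Intention to treat does not require imputation on top of that. If the gaps are filled first, a score from as early as week 0 or week 2 stands in for week 12, the model no longer sees any missing data, and the missing-at-random assumption gives way to the assumption that nothing changes after a participant leaves. In a trial where both arms receive routine care, and where the effect may build up over 12 weeks, that assumption has no support in the protocol. The filled values also count as measured data, which makes the standard error too small.

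At stake is the primary week-12 difference. Some withdrawal reasons in section 9.2 may be related to treatment, so unequal dropout is plausible, although the protocol gives no split by arm.

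**Working it through.** **The plan's own figure.** Inputs from section 11.3: difference 7, SD 14.3, "With an alpha value of 0.05, and power of 0.8"; two-sided test from section 11.4.

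n per arm = 2 × (1.960 + 0.842)² × 14.3² / 7² = 65.5, so 66 per arm and 132 in all, as stated. Allowing for attrition, 132 / 0.85 = 155.3, so 156, close to the stated 160 or so. At 15% of 160, about 24 participants would have a carried-forward score entered as week 12.

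**Assumptions not in the documents.** Change is linear over 12 weeks. The placebo arm improves by 10 points unless stated otherwise. Dropouts' last visits are spread evenly over weeks 0, 2, 4, 6, 8 and 10 (mean week 5), or over weeks 0, 2 and 4 for early dropout (mean week 2). Dropout by arm is as listed.

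**Expected carried-forward improvement in an arm** with 12-week improvement D and dropout d is D × [(1 − d) + d × f], where f = 5/12 for spread dropout and f = 2/12 for early dropout. Below, positive differences favour active, and dropout is given as active v placebo.

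- True effect 7, 15% v 15%, spread: 7 × (0.85 + 0.15 × 5/12) = 6.4.
- True effect 7, 20% v 10%, spread: 17 × 0.8833 − 10 × 0.9417 = 15.0 − 9.4 = 5.6.
- True effect 7, 10% v 20%, spread: 17 × 0.9417 − 10 × 0.8833 = 16.0 − 8.8 = 7.2. With 5 points of placebo improvement instead: 12 × 0.9417 − 5 × 0.8833 = 11.3 − 4.4 = 6.9.
- True effect 7, 5% v 25%, spread: 17 × 0.9708 − 10 × 0.8542 = 16.5 − 8.5 = 8.0.
- True effect 7, 25% v 10%, early: 17 × 0.7917 − 10 × 0.9167 = 13.5 − 9.2 = 4.3.
- No effect, equal dropout: 0.
- No effect, 20% v 10%, spread: 8.83 − 9.42 = −0.58, against active.
- No effect, 25% v 10%, early: 7.92 − 9.17 = −1.25, against active.

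**Test behaviour by simulation.** Setting: 80 per arm, SD 14.3, correlation 0.3 + 0.6 × 0.9^lag between visits, baseline-adjusted comparison at week 12, 10 points of placebo improvement, dropout unrelated to the scores. The comparator uses only observed week-12 scores under the same dropout.

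| Case | Carried forward | Observed week-12 scores |
|---|---|---|
| Effect 7, 15% v 15% | estimate 6.4, power about 94% | power about 94% |
| No effect, 15% v 15% | no bias, type I error just under 5% | – |
| No effect, 20% v 10% | bias about 0.6, type I error about 6% | – |
| No effect, 25% v 10% early | bias about 1.2, type I error 10-11% | – |
| Effect 7, 25% v 10% early | estimate 4.3, power about 63% | power about 94% |

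Halving the common improvement to 5 points roughly halves the bias under no effect: about 0.3 at 20% v 10%, with type I error between 5% and 6%.

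**The protocol's own model.** The random-intercept model with baseline covariate was fitted to filled and to observed data (600 runs, true effect 7, placebo improvement 5, 15% v 15%). It gave about 6.4 on filled data and 7.0 on observed data, whether dropout was random or depended on the last observed score. The mean reported standard error was about 1.63 on filled data and 1.73 on observed data under random dropout.

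**The case against.** The strongest objection is that section 11.4 does not say that carrying forward comes before the MMRM. It has one sentence on intention to treat and another on the model, and an analysis plan not shown here might settle which data the model receives. That stands as far as it goes: the order is inferred. But the rule covers the study outcomes and no other efficacy analysis exists for it to feed. If something else was meant, the section is still ambiguous about the primary analysis and needs the same edit.

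The second objection is about size, and most of it stands. At the only attrition figure the protocol gives, split equally, the estimate shrinks by about 0.6 points, almost no power is lost, and type I error holds. Even that shrinkage needs an effect still accruing when participants leave. Some unequal splits nearly cancel: at 10% active v 20% placebo, a true 7 is estimated at 6.9 to 7.2. The larger figures need 25% v 10% dropout, all by week 4, and 10 points of common improvement, none of which is in the protocol.

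Three stronger inferences are tempting and not supported:

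- That the primary estimate is necessarily biased. It is not under equal dropout with no effect, or if scores are stable.
- That carrying forward costs the whole gap between 63% power and the power of a trial with no dropout. Part of that gap is loss of patients; the fair comparator is about 94%.
- That rejection rates simulated under the planned model (15-23% with no effect, 10 points of improvement and 5% v 25% dropout in either direction) are all due to carrying forward. The same model on observed data rejected in 8-10% of runs, because of its random-intercept covariance, which is a separate matter.

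**Conclusion.** The point holds in conditional form. As written, section 11.4 sets a no-change-after-dropout rule beside an MMRM that does not need it, and the natural reading lets filled scores enter the week-12 comparison. At 15% attrition in both arms the harm is modest: about 6.4 for a true 7, and none under no effect. If dropout differs by arm, the estimate is generally biased and can favour either arm, so carrying forward cannot be defended as conservative. The illustrated range runs from near-cancellation, through a bias of about 0.6 points at 20% v 10% dropout with no effect, to an estimate of 4.3 for a true 7 at 25% v 10% early dropout. These sizes rest on assumed linear trajectories, dropout timing and splits by arm. The direction and amount in this trial cannot be known from the protocol. Because the protocol fixes the rule and does not leave it open, an analysis plan using observed data only would contradict it.

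**What to change.** In section 11.4, delete the parenthesis that defines intention to treat by carrying forward. State that the primary MMRM is fitted to all observed post-baseline PANSS total scores of all randomised participants, without imputation, and that the week-12 treatment difference from that model is primary. Keep carrying forward, if at all, only as a labelled sensitivity analysis.

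The cost is a change of wording. No extra data are needed and the sample size is unaffected. The reported standard error will be slightly larger (about 1.73 against 1.63 in the case above), because filled values no longer count as measurements.

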## 3 Study Design

The design is a randomised, placebo-controlled, double-blind parallel-group trial to examine the clinical efficacy and safety of add-on treatment of sodium benzoate for persistent symptoms in patients with early psychosis. The study will include 160 individuals with first episode psychosis.

Participants will be given either 1g/d (500mg twice daily) of sodium benzoate or placebo, in addition to their normal routine care. Routine care is defined as 'individualized combinations of psychopharmacology, behavioural interventions, rehabilitation and associated clinical services in keeping with Queensland Health standards of care'

Face to face clinical assessments will be at baseline (week 0) and weeks 2, 4, 6, 8, 10 and 12. Weekly phone contact (if no phone then face to face assessment) will occur in between face to face visits. A post-completion visit will be conducted at week 14. Randomisation will be carried out using a computer-generated randomization table, stratified by five sites. Each of the five sites will have separate randomization tables, and each list will ensure randomization is blocked in groups of four. Participants will receive either active treatment or placebo in a 1:1 ratio.

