## 7.5 Randomisation Procedure

Participants will be randomised once written consent has been obtained and the baseline assessments have been completed. Participants will be randomised to one of the treatment groups, using blocks of 4 via a computer-generated randomization table. Randomisation will be stratified by five sites (a) Metro North HHS, (b) Metro South HHS, (c) West Moreton HHS, (d) Gold Coast HHS, and (e) Children's Health Queensland HHS. Participants will receive either active treatment or placebo in a 1:1 ratio.

The investigational products will be manufactured in accordance with current Good Manufacturing Practice (GMP) in a suitable TGA licensed facility. This same company (Pharmaceutical Packing Professionals) will hold the randomisation code, and provide a 24 hour

1800 number to unblind participants if required. Participants will be randomised strictly using a chronological process. Participants will be allocated a unique identification number which will be linked to the specific site number. If a participant withdraws from the study then the participant number will not be re-used nor will the participant be allowed to re-enter the study.

The randomisation will be double-blind. An independent Biostatistician will generate the randomisation list which will be provided to the manufacturer. The independent manufacturer will hold the closed randomisation list and be the only one who has the ability to unblind. In the case of emergency where it is crucial the medical staff knows whether the participant is on sodium benzoate or placebo, participants will be provided with contact information (i.e. 24 hour 1800 number) for unblinding.

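### Randomisation is stratified by five sites but the stated efficacy model has no site term, which may cost a modest amount of precision

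*Protocol*

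**What the plan says.** Protocol section 3 describes the allocation: "Randomisation will be carried out using a computer-generated randomization table, stratified by five sites". Each site has a separate table, and "each list will ensure randomization is blocked in groups of four". Section 7.5 repeats the design ("Randomisation will be stratified by five sites") and names the five Hospital and Health Services, one of which is a children's service. Allocation is 1:1.

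Section 11.4 specifies the efficacy analysis as a repeated-measures mixed model "with treatment, week, and treatment-week interaction as fixed effects", with "intercept as the only random effect; baseline value will be the covariant". Site is neither a fixed nor a random term there, and no other section adds it. Tests are two-sided at 0.05 ("values will be based on 2-tailored tests with significance levels of 0.05").

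Section 11.3 sizes the trial "With an alpha value of 0.05, and power of 0.8" to detect a "difference in mean PANSS Total of at least 7 units", using an SD of 14.3. It arrives at 66 per group and, with 15% attrition, about 160 randomised. Site plays no part in that calculation.

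**The concern.** Blocking within site makes the arms nearly equal in number at every site, so differences between sites largely cancel out of the treatment comparison. A model without site does not know this. It leaves the between-site variation in the between-participant variance. The random intercept, read as a participant intercept, absorbs that variation but does not take it out of the standard error of the treatment effect. The reported standard error then exceeds the true one, the confidence interval is too wide, and the test rejects less often than its nominal level.

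At stake is precision that the stratified design has already bought. How much depends on how far sites still differ in outcome once baseline has been adjusted for.

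**Working it through.** **Inputs from the protocol.** Difference 7, SD 14.3, power 0.80 and 66 per group (section 11.3); two-sided alpha 0.05 (sections 11.3 and 11.4); five sites, blocks of four, 1:1 (sections 3 and 7.5).

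**Input not in the protocol.** ρ, the share of residual outcome variance lying between sites. It is an assumption, shown from 0% to 15%.

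**Step 1: reproduce the planned size.** n per arm = 2 × (1.960 + 0.842)² × 14.3² / 7² = 65.5, rounded up to 66 (132 in total). Allowing for attrition, 132 / 0.85 = 155.3, or 156 in two equal arms, consistent with the stated figure of about 160. The standard error of the difference is 14.3 × √(2/66) = 2.489, so the standardised difference is 7 / 2.489 = 2.812 and power is Φ(2.812 − 1.960) = 80.3%. With the noncentral t distribution it is 79.7%.

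**Step 2: effect of leaving site out.** Hold the total SD at 14.3 and treat the arms as balanced within site. The true standard error is then √(1 − ρ) times the one reported by a model without site.

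- Type I error without site = 2 × [1 − Φ(1.960 / √(1 − ρ))]
- Power without site = Φ((2.812 − 1.960) / √(1 − ρ))
- Power with site = Φ(2.812 / √(1 − ρ) − 1.960)

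For ρ = 10%, √0.90 = 0.949. Type I error is 2 × [1 − Φ(2.066)] = 3.9%, power without site is Φ(0.898) = 81.5%, and power with site is Φ(1.004) = 84.2%.

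| Assumed site share ρ | Reported SE too large by | Type I error without site | Power without site | Power with site | n per arm for 80% power with site |
|---|---|---|---|---|---|
| 0% | 0% | 5.0% | 80.3% | 80.3% | 66 |
| 2% | 1.0% | 4.8% | 80.5% | 81.1% | 65 |
| 5% | 2.6% | 4.4% | 80.9% | 82.3% | 63 |
| 10% | 5.4% | 3.9% | 81.5% | 84.2% | 59 |
| 15% | 8.5% | 3.4% | 82.2% | 86.2% | 56 |

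Power without site rises slightly down the table because the total SD is held fixed, so a larger site share means less variation within sites.

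**Step 3: simulation.** 20,000 trials per setting, 132 participants, five uneven sites (44, 36, 28, 16 and 8, an assumption), blocks of four, one final outcome, t tests.

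- ρ = 10%: mean reported SE without site 2.49 against an empirical 2.36 to 2.38; type I error 3.9% without site and 5.0% with it; power 80.6% and 83.6%.
- ρ = 5%: type I error 4.3% and 4.9%; power 80.1% and 81.7%.

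The simulated powers lie a little below the table because of the t distribution and the degrees of freedom spent on site. Direction and size agree.

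**The case against.** The strongest case against is that little is at stake. The gain from adding site runs from nothing at ρ = 0% to about 4 points of power at ρ = 15%, on top of a target that the stated model already meets. That stands.

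Nor do the documents show that sites differ. A reader might infer it from the children's service, the individualised routine care and the clinician-rated outcome. But the protocol gives no outcome data by site, no enrolment per site and no assignment of raters. Some of it points the other way: a 30-participant training phase for inter-rater reliability (section 6), one set of eligibility criteria (section 4), a common state standard for routine care (sections 3 and 7.3), and a baseline covariate that absorbs site differences in severity as far as baseline predicts outcome. Site differences are plausible, not established, and the 10% and 15% rows have no documentary support.

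The sums are also not for the protocol's own model. Section 11.4 specifies repeated measures with a random intercept only, which pools variance over visits, on data with last observation carried forward. If week-12 variance were 10% above the pooled value (an assumption), type I error would be 2 × [1 − Φ(1.960 / √1.10)] = 6.2% with no site effect, and 2 × [1 − Φ(1.960 / √(1.10 × 0.95))] = 5.5% with a 5% site share. So the claim that the test is conservative holds only with the other model features correct. That qualification stands too.

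Finally, the protocol says only of the random effect, not of the fixed effects, and an analysis plan that is not shown might add site. This is fair as far as it goes. Even so, the protocol does not leave the model open: it names the fixed effects, the random effect, the covariate and the software procedure, and on its natural reading site is absent.

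**Conclusion.** The omission is certain on the protocol's text; its size is not. If sites differ in outcome after baseline adjustment, and the other model features are correct, the standard error of the treatment effect is overstated and the test is conservative. Over assumed site shares of 2% to 15%, true type I error falls from 4.8% to 3.4%, and the power forgone is about 0.5 to 4 percentage points. With no site variation the loss is nil.

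Two stronger readings are tempting. One is that ignoring the strata invalidates the primary test. It does not: leaving site out neither biases the treatment estimate nor inflates type I error, so a positive result would not be undermined by it. The other is that the trial is underpowered as a result. It is not: by the protocol's own calculation, power without site is 80.3% or more at every share considered, and the 79.7% from the t distribution at zero site variation has nothing to do with site.

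This is a modest, nearly free improvement. It rests on an assumed site share, on 14.3 as the residual SD (baseline adjustment would shrink it with or without site in the model), on a single final outcome, and on reading the unlabelled random intercept as a participant intercept.

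**What to change.** In section 11.4, add site, defined as the five randomisation strata, as a fixed effect in the mixed model for the primary and secondary outcomes. State before unblinding how any very small site will be pooled, so that neither the pooling nor the choice between an adjusted and an unadjusted result can follow the data.

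The cost is one model term and up to 4 degrees of freedom. No new data are needed and the sample size need not change.
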